## Methods

### Patients

Female patients over the age of 18, with a recent diagnosis of breast cancer and scheduled for adjuvant treatment in the form of chemotherapy, radiation therapy and/or hormonal therapy are eligible for this study and will consecutively be included in the project. Patients will be recruited from three hospitals in the central part of Sweden (Uppsala, Gävle and Falun). Criteria for exclusion are an ongoing psychiatric condition or language deficiencies in Swedish. According to the power calculations, a total sample of 300 patients is necessary.

### Design

The study is a prospective longitudinal intervention study with a stepped-care approach [13], where patients will be randomised to one of two interventions in the final stage of treatment. One of the key concepts in the stepped-care model is that the needs of the individual are matched to the appropriate level of care [13]. The first step is a low intensity intervention that is given to all patients. Patients who do not respond to this level are thereafter given more intensive treatment at later steps in the program. Since methods from CBT (cognitive behavior therapy) have already been shown not only to reduce the risk for PTSD [8] but also to have a positive effect on quality of life and psychological well being for patients with breast cancer [9,14], there is no control group in the study. All patients (n = 300) will receive the first level of the intervention program. All patients (estimated to n = 150) who continue to report stress symptoms after the first step of the intervention program will be given the chance to participate in the second step of the program. The second step includes randomisation to one of two treatments: a stress management group or individual stress management (See Figure 1). With this design it will be possible to study the prevalence of stress related symptoms as well as to study which factors predict which patients will be Clinically Significant Improved (CSI) with a basic level of education about stress management. In addition the study will help to identify those patients who need additional help and to compare the effects of individual and group interventions.

**Figure 1 F1:**
[figure not shown]
Study design.

### Intervention

All patients start at the first step of the intervention program and receive detailed information about different stress symptoms and different ways to deal with them. Patients will be given the opportunity to ask questions and will receive written material to be read at home. All patients are evaluated at the end of the intervention (Table 1) to see if they are clinically significant improved (CSI). CSI is defined as a decrease in stress related symptoms as measured by Impact of Event Scale (IES) and/or the Hospital and Depression Scale (HADS) from clinical levels to normal results. Patients who are evaluated as CSI as well as patients who did not report clinical levels on IES or HADS at the start of the intervention leave the program but are followed up during the coming year (Table 1). The remaining patients will be asked if they wish to continue in the program to the next step. Those patients who wish to continue will be randomised to group (Step 2a) or individual stress management (Step 2b). Within a week after randomisation patients will be contacted by telephone to receive information about which group they are assigned to and practical details about the start of the intervention.

**Table 1 T1:** Summary of interventions and measures used at repeated points in time

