
This paper presents the design of a randomized multi-centre trial to evaluate the effectiveness and cost-effectiveness of a stress management intervention using a stepped- care approach. The first step is a low intensity intervention that is given to all patients. Patients who do not respond to this level are thereafter given more intensive treatment at step 2 in the program. They will in step 2 be randomised to more intensive stress-management intervention in a group setting or individual. The hypothesis is that half of the individuals assigned to a low intensity intervention will be significantly improved after treatment. For individuals who continue to have symptoms after low intensity treatment it is hypothesized that continued treatment in a group setting with high intensity interventions will be more cost-effective. In addition the assumption is that reduction of stress symptoms in women with breast cancer will lead to a reduction in socio-economic costs.

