### Data analysis

SPSS® ANOVA will be used to analyze differences between groups and for repeated measures over time for the continuous variables while nominal (categorical) variables will be tested with chi square (exact). Although not all the criteria for normal distribution are met by this selection the parametric tests are robust enough to be used. Patients’ levels of stress related symptoms will be categorized according to recognized cut-off points (See references in Table 1). A hierarchical linear regression analysis will be used to examine which variables predict stress symptoms and utilization of health care services as well as sick leave and return to work. Power calculations have been done for IES based on data from Support Project. On the basis of these conditions (power = 0.8, p = .05 and effect size = 0.59) at least 64 patients must be included in each group (i.e. a total of 128) patients) to detect a significant difference on IES.

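### Clinically significant improvement (CSI) is defined only by moving from clinical to normal, with no minimum or reliable change, although its predictors are a study aim

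*Protocol article*

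**What the plan says.** The protocol article, Methods, Intervention, gives an operational rule: "CSI is defined as a decrease in stress related symptoms as measured by Impact of Event Scale (IES") and/or HADS, "from clinical levels to normal results". No size of decrease is attached. The evaluation follows Step 1: "All patients are evaluated at the end of the intervention (Table 1) to see if they are clinically significant improved (CSI"). Table 1 places the relevant IES and HADS measurements at inclusion and 3 months after inclusion.

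The Data analysis section says that "Patients’ levels of stress related symptoms will be categorized according to recognized cut-off points". It refers to the Table 1 references for these and prints no values.

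CSI status has two uses:

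- **Routing (Intervention).** Women who are CSI leave the program and are followed up, as do women who were not at clinical level at the start. The rest are offered randomisation in Step 2.
- **Research aim (Design).** The design is meant to make it possible "to study which factors predict which patients will be Clinically Significant Improved (CSI) with a basic level of education about stress management".

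The Background hypothesis is that "half of the individuals assigned to a low intensity intervention will be significantly improved after treatment". It does not name CSI, but CSI is the only criterion of improvement that the article defines for that step.

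**The concern.** The label says that an individual woman has improved by an amount that matters. The rule establishes only that her category changed. A score that wobbles around a threshold changes category without any demonstrable change in the woman, and nothing in the definition screens this out.

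Two things are at stake:

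- **The Step 1 response rate.** Part of any reported CSI rate will be crossings within measurement error.
- **The predictor analysis.** The closer a woman starts to the threshold, the less she has to change to qualify. Her inclusion score then predicts CSI for a purely arithmetical reason, and any factor correlated with the inclusion score inherits part of that association. A model without the inclusion score would partly rediscover distance to the cut-off.

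This is a weakness of the individual-level definition. It would remain if Step 1 had a comparator.

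**Working it through.** The article gives no figure for this point, so there is none to reproduce. The check is a logical step followed by an illustration on stated assumptions.

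**Logic.** CSI requires a clinical score at inclusion, a normal score at 3 months and a decrease between them. The smallest qualifying decrease is therefore the distance between the lowest clinical score and the highest normal score. With a single cut-off this is one point. With an unclassified band between the two categories it is about the width of that band. The article does not say which applies.

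**Inputs.**

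- Share at clinical level at inclusion: 80%. This is borrowed from the earlier study described in the Background, where 80% initially reported a high level of stress symptoms. The article does not say that this was an IES cut-off.
- Correlation r between inclusion and 3 months: 0.6 to 0.9 (assumed).
- Normal scores with SD 1 and no change in the mean (assumed).
- IES only.

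**Model.** x is the inclusion score, standard normal, and y = r·x + √(1 − r²)·e is the 3-month score, with e standard normal and independent of x. The cut-off is c = Φ⁻¹(0.20) = −0.842. CSI means x ≥ c and y < c − g, where g is the gap between clinical and normal. There were 2,000,000 simulated pairs per scenario.

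**Reliable change (Jacobson-Truax).** RC = 1.96 × SD × √(2(1 − reliability)). Two versions bracket the answer:

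- Reliability equal to r, which treats all 3-month instability as measurement error.
- Reliability 0.9, which gives RC = 1.96 × √0.2 = 0.877 SD and lets some of the 3-month instability be real individual change.

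| r | CSI, g = 0 | of these below RC, reliability = r | of these below RC, reliability = 0.9 | CSI, g = 0.5 SD |
|---|---|---|---|---|
| 0.9 | 6% | 85% | 85% | 1% |
| 0.8 | 9% | 86% | 62% | 2% |
| 0.7 | 11% | 86% | 48% | 3% |
| 0.6 | 13% | 86% | 38% | 4% |

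CSI rates are percentages of women at clinical level at inclusion. With one cut-off, requiring reliable change as well as crossing leaves 1% to 2% if reliability equals r, and 1% to 8% (r = 0.9 down to 0.6) if reliability is 0.9.

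**Dependence on the starting score.** Take one cut-off, r = 0.8 and no mean change. Given x, the probability of CSI is Φ((c − 0.8x)/√(1 − 0.64)) = Φ((c − 0.8x)/0.6).

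- x = −0.6 (0.24 SD above the cut-off): Φ((−0.842 + 0.48)/0.6) = Φ(−0.60) = 27%.
- x = 0.5 (1.34 SD above the cut-off): Φ((−0.842 − 0.40)/0.6) = Φ(−2.07) = 2%.

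Under these assumptions the inclusion score alone moves the chance of CSI more than tenfold, with no treatment effect on the mean.

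**The case against.** **One cut-off is an inference.** A reader might conclude that the plan uses the same score as the lower limit of clinical and the upper limit of normal. The article does not say so. It speaks of cut-off points in the plural and leaves their values to references. The one-point example and the 6% to 13% are conditional on a single cut-off, and a gap of 0.5 SD cuts the rate to 1% to 4%. This objection stands and limits the size. It does not remove the point, because the definition has no minimum change whatever the cut-offs are.

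**Large falls that stay above the cut-off.** It is tempting to add that a woman with a large fall who ends at clinical level is wrongly denied CSI. The article does not support that complaint. Under stepped care matched to individual need, a woman still at clinical level still has need, and a normal end state is a legitimate criterion. The fix below keeps it.

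**CSI has a limited role.** The primary outcome is IES, analysed as a continuous variable. The regression in the Data analysis section does not name CSI, and neither does the Background hypothesis. This is right, and it rules out calling CSI the declared outcome of the Step 1 hypothesis. The Design section, however, does name prediction of CSI as something the study is for. The predictor model is not written out in the article, so its missing covariates are no fault in themselves. What is open to criticism is the stated outcome definition that the model would use.

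**The share below reliable change depends on an assumption.** Using the 3-month correlation as reliability counts real individual change as error, and so yields about 85% almost by construction. With reliability 0.9 the share is 38% to 62% for r = 0.6 to 0.8. Hence the range of about 40% to 85%.

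**HADS.** One might infer that the second scale inflates the rate further. That holds only if normalising on either scale is enough while the other may stay clinical, and the and/or wording does not settle this. No size is claimed for it here.

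**Conclusion.** The point holds in a limited form. CSI is a pure change of category with no minimum or reliable change, so the label claims more about the individual than the rule shows. If one cut-off bounds both categories, a one-point move qualifies, and distance to the cut-off becomes a mechanical predictor of an outcome whose predictors the study means to identify.

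The size is moderate. It is 6% to 13% of women at clinical level with one cut-off and no mean change, and about 1% to 4% with a gap of 0.5 SD, to be read against a hypothesised half improved. Normality, the correlation, the reliability and the transfer of the earlier study's 80% are all assumptions.

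A reader might infer that the randomised comparison of group and individual treatment on IES is undermined. It is not: that comparison uses the continuous score and does not depend on CSI as an endpoint. The Step 1 improvement rate and the CSI predictor results are what is affected.

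**What to change.** Leave the rule that routes patients between steps as it is. For the reported endpoint:

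1. State the cut-off values for clinical and for normal on each scale, and whether there is a range between them.
2. Report the Step 1 result in two forms side by side: the crossing rate as now defined, and the rate of crossing plus a decrease larger than a pre-stated reliable change, 1.96 × SD × √(2(1 − reliability)). Use the scale's measurement reliability rather than the 3-month correlation, and the SD from the earlier study, whose IES data already served for the power calculation.
3. Use crossing plus reliable change as the outcome in the model for predictors of CSI, and include the inclusion score as a covariate.

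The cost is some analysis wording and one derived variable from scores already collected at inclusion and 3 months. There are two downsides. The reported improvement rate will be lower. Some women who left the program as CSI will also not meet the reliable-change version, so routing status and reported endpoint will differ for them. The report should say so and give their number.

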		***Time of assessment***				
***Questionnaire***	**Inclusion**	*Intervention* *Step 1*	**3 months after inclusion**	*Interventions* *Step 2*	**1 month after completed intervention**	**12 months after completed intervention**
*n*	*300*	*300*	*300*	*150*	*150*	*300*
IES [15]	X		X		X	X
HADS [16]	X		X		X	X
EORTC QLQ C-30 [17]	X		X		X	X
EORTC QLQ BR-23 [18]	X		X		X	X
EQ-5D [19]	X		X		X	X
MFI [20,21]	X		X		X	X
Stress in daily living [22]	X		X		X	X
Self-reported sick leave and use of other professional services	X		X		X	X
Background data	X					X
Patient satisfaction with interventions [11]			X		X	X
PGPQ [23] (n = 150)			X		X	X

### Intervention, Step 2

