**Method:**

Female patients over the age of 18, with a recent diagnosis of breast cancer and scheduled for adjuvant treatment in the form of chemotherapy, radiation therapy and/or hormonal therapy are eligible and will consecutively be included in the study. The study is a prospective longitudinal intervention study with a stepped-care approach, where patients will be randomised to one of two interventions in the final stage of treatment. The first step is a low intensity stress-management intervention that is given to all patients. Patients who do not respond to this level are thereafter given more intensive treatment at later steps in the program and will be randomized to more intensive stress-management intervention in a group setting or individually. The primary out-come is subjective distress (intrusion and avoidance) assessed by the Impact of Event Scale (IES). According to the power-analyses, 300 patients are planned to be included in the study and will be followed for one year. Other outcomes are anxiety, depression, quality of life, fatigue, stress in daily living and utilization of hospital services. This will be assessed with well-known psychometric tested questionnaires. Also, the cost-effectiveness of the intervention given in group or individually will be evaluated.

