The research group “Support project” has studied the effect of individual counselling conducted by a specially trained nurse [9]. This intervention was compared to the results of therapy conducted by a psychologist and to a group that received treatment as usual. The project started in 1997 with special training for nurses [10]. The project continued during for the next 5 years and data collection was concluded in January 2002. Patients in this study had been diagnosed with breast cancer and were offered adjuvant treatment. A total of 179 patients were consecutively included. The results showed that both active treatments had a positive effect, measured in terms of increased HRQoL and decreased symptoms of stress (e.g. intrusive thoughts) in comparison to the control group who received treatment as usual [9]. More patients in the control group took advantage of the psychosocial support that was available for all patients in standard care as compared to both intervention groups. The level of satisfaction was generally high in both intervention groups [11]. However patients in the nurse-counselor groups reported that greater satisfaction with interventions for worry, information about their illness, prognosis, tests, treatment as well as general contact with health care facilities than patients in the psychologist groups. Utilization of health care and number of days on sick leave can be attributed to the adjuvant treatment [12]. Both the intervention groups had lower total costs for medical care than the control group who required more days for in-patient care. The conclusions that can be drawn from this study are that the psychosocial interventions were useful for breast cancer patients, that they were relatively inexpensive and that interventions offered by nurses were as effective as those given by psychologists. The results of the “Support Project” described above generated additional questions. Most patients reported relatively high levels of HRQoL as well as relatively low levels of symptoms and side-effects of their illness and treatment. Despite these findings 75% of the patients reported that they had problems for which the psychosocial interventions provided help. A more detailed analysis of the data showed that 80% of the patients in the study reported a high level of stress symptoms initially, such as intrusive thoughts and avoidance behavior. These symptoms remained high throughout the study. Other symptoms such as worry and depression were also reported at high levels initially but these symptoms had decreased to normal levels after 3 months. This indicates that here is a need for closer examination of other factors for breast cancer patients, such as stress-related symptoms and behavior, predictors for stress, effects on role and social functions as well as utilization of heath care, sick leave and return to work settings. In addition there is a need to study how psychosocial interventions with a focus on stress management can influence the above-mentioned factors.

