#### Step 2a

Stress management, group format. Participants (6–8 patients/group) will meet for 2 hours every week for a total of 20 hours. In the intervals between the group meetings patients will be asked to do homework. This homework can entail practicing problem-solving techniques, keeping a diary, practicing relaxation or participating in physical activities. Each group meeting has a specific subject, derived from the 6 components in the intervention [24]. These components concern 1) basic knowledge about cancer, treatment, healthy living and stress reactions, 2) self-awareness with the help of a diary for thoughts, feelings and behavior, as well as group discussions of specific cases 3) instruction in various techniques about how to express negative feelings, how to communicate with others more effectively how to change behaviors related to stress, anger, worry and depression 4) training these techniques in real-life situations outside the group, 5) cognitive restructuring with the help of diaries, techniques and group dynamics and 6) spirituality, in a broad sense, with group discussions of quality of life, values, self-confidence and optimism. Written materials, case studies and video presentations will be used.

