### Step 2b Individual intervention

The methods and techniques will be the same as those used in the group intervention. The first session will be used for a detailed assessment of the individual’s psychosocial problems, as used in earlier studies [9,11]. The sessions will last 45–60 minutes. The number of sessions will depend on the individual patient’s problems and the joint assessment made by the patient and nurse together. The total number of sessions will be at least 4, with a maximum of 8. The contents of the sessions are Session 1: Assessment, Session 2: Analysis of diary (self-registration) and suggestions for problem management, Session 3: Evaluation of problem management skills Session 4: Follow-up and conclusion of the intervention. When necessary Sessions 5–8 will address specific obstacles and continued practice.

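### Both Step 2 follow-ups are timed from completion of treatment, which comes at a different time in each arm and, in the individual arm, depends on patient need

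*Protocol article*

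**What the plan says.** Table 1 has two assessment columns after Step 2, headed "1 month after completed intervention" and "12 months after completed intervention". IES, HADS, EQ-5D, the quality-of-life and fatigue questionnaires, and self-reported sick leave and service use are all collected at both. No assessment after Step 2 is fixed from randomisation or from inclusion. The Abstract says that patients "will be followed for one year" without giving a starting point.

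Randomisation comes before Step 2 (Methods, Intervention). After it the two programmes differ in length:

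- Group (Step 2a): patients, in groups of 6 to 8, "will meet for 2 hours every week for a total of 20 hours".
- Individual (Step 2b): "The total number of sessions will be at least 4, with a maximum of 8". How many a patient receives is decided along the way: "The number of sessions will depend on the individual patient’s problems and the joint assessment made by the patient and nurse together". The interval between sessions is not stated.

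The Abstract plans a cost-effectiveness comparison of the two formats, and the Background hypothesises that the group format will be the more cost-effective. Hospital use is to come from the hospitals' computer systems (Data collection), with no window stated.

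**The concern.** The follow-up clock starts at an event that occurs after randomisation and is shaped by the treatment itself. In the group arm the time to that event is fixed once the group starts. In the individual arm, a patient with more problems has more sessions and is therefore assessed later. The arms are then compared at different times since randomisation and diagnosis, and part of any observed difference may reflect timing rather than format.

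The article's own account of the earlier Support Project shows that some of these outcomes follow the course of illness and treatment. Worry and depression fell to normal levels after 3 months, and "Utilization of health care and number of days on sick leave can be attributed to the adjuvant treatment". Costs, service use and sick leave counted from randomisation to the last assessment would also cover windows of unequal length. A comparison that includes the cost of the intervention itself has to start at randomisation or at the start of Step 2, so the unequal stretch cannot simply be left out.

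**Working it through.** The article calculates no assessment times, so there is no planned figure to reproduce beyond the length of the group programme.

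**Inputs from the article**
- Group arm: 20 h / 2 h per week = 10 weekly meetings, so (10 - 1) x 1 = 9 weeks from first to last.
- Individual arm: k = 4 to 8 sessions.
- Assessments 1 and 12 months after completion. With 365.25/12/7 = 4.35 weeks per month, these are 4.35 and 52.2 weeks.

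**Assumptions, not in the article**
- Individual sessions are s = 1, 2 or 3 weeks apart.
- Both arms start Step 2 equally soon after randomisation (no wait to form a group).

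**Formulas**
- End of the individual programme, in weeks from its start: (k - 1) x s.
- Individual minus group, the same at both assessments: D = (k - 1) x s - 9.

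The group arm is assessed at 9 + 4.35 = 13.3 weeks and 9 + 52.2 = 61.2 weeks from the start of Step 2.

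| Assumed spacing | Individual programme ends (k = 4 to 8) | 1-month assessment | 12-month assessment | D (weeks) |
|---|---|---|---|---|
| Weekly | 3 to 7 | 7.3 to 11.3 | 55.2 to 59.2 | -6 to -2 |
| Every 2 weeks | 6 to 14 | 10.3 to 18.3 | 58.2 to 66.2 | -3 to +5 |
| Every 3 weeks | 9 to 21 | 13.3 to 25.3 | 61.2 to 73.2 | 0 to +12 |

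**Relative size**
- Last assessment: -6/61.2 = -10% to +12/61.2 = +20%.
- 1-month assessment: -6/13.3 = -45% to +12/13.3 = +90%.

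**Can one spacing align the arms?** D = 0 requires s = 9/(k - 1): 3.0 weeks for 4 sessions, 1.8 for 6 and 1.3 for 8. No single spacing works for all patients. Within the individual arm, patients with 4 and with 8 sessions differ by 4 x s, which is 4, 8 or 12 weeks.

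**Effect of a group wait.** If the group arm waits w weeks longer to start, D becomes (k - 1) x s - 9 - w. The article gives no value for w.

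**Final column of Table 1.** Its n = 300 combines Step 1 leavers with Step 2 patients. If Step 2 starts at the 3-month assessment, a group-arm patient reaches this column about 3 + 2.1 + 12 = 17.1 months after inclusion. A Step 1 leaver whose clock starts when Step 1 ends, within the first 3 months, reaches it by about 15 months.

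**The case against.** The case on the other side has real weight.

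- **Direction.** A reader might infer that the group window must be the longer one, because its programme is long and a group has to be filled. The article does not support this. With fortnightly or three-weekly individual sessions, the individual window can equal or exceed it. The article does not say that groups wait or that individual treatment starts at once. Patients in both arms are telephoned within a week of randomisation with practical details of the start. This objection stands.
- **Primary outcome.** A reader might infer that the IES comparison is seriously compromised. The Background reports that intrusion and avoidance stayed high throughout the earlier study, so a shift of some weeks probably matters less there. The fall in worry and depression after 3 months also covers roughly the period before Step 2 begins. Both points stand.
- **Non-completers.** A reader might infer that they drop out of follow-up. Nothing says so: questionnaires are posted to patients' homes with telephone contact after 14 days, and none of this is restricted to completers. What remains is only that a date counted from completion is undefined for someone who does not complete.
- **Costs.** The 11 months between the two later assessments are equal in both arms, and hospital data can be cut to any common window. That is true. Self-reported sick leave and other service use, however, are collected at the completion-based dates.
- **Step 1 leavers.** They are outside the randomised comparison and cannot bias it. This stands; their timing matters only where all 300 patients are analysed together.
- **Purpose.** Timing from the end of treatment answers a legitimate question, and a fixed early date could fall in mid-programme for some patients. This is a good reason to leave the 1-month assessment where it is.

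**Conclusion.** The point holds as a design weakness in something the article fixes, not something it omits. Under Table 1 as written, time from randomisation to outcome depends on arm and, in the individual arm, on need-driven treatment length. This follows from the stated programme lengths and needs no assumption.

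The size does rest on assumptions. With spacings of one to three weeks and no group wait, the gap runs from -6 to +12 weeks, or about -10% to +20% of the window to the last assessment. It is proportionally larger at the 1-month assessment. With weekly sessions the gap at the last assessment is modest, 2 to 6 weeks in about 61. Neither the direction nor the average gap can be determined from the article.

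The consequence falls mainly on the group-versus-individual cost-effectiveness comparison, sick leave, service use and the secondary outcomes, and less on IES. The article does not support a claim of a necessarily longer group window or of lost non-completers.

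**What to change.** 1. Set the final Step 2 assessment at one fixed time from randomisation in both arms, late enough to follow the longest programme.
2. Post it to every randomised patient, whether or not the programme was completed.
3. Count costs, service use and sick leave over that same window from randomisation.
4. Keep the questionnaire 1 month after completion as an end-of-treatment measure. Record the actual time since randomisation and report it by arm.
5. Report Step 1 leavers separately, or assess them at a matched time from inclusion.

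The cost is small: changed mailing dates, a new heading in Table 1 and one definition of the cost window. The questionnaires are already posted, so no visits are added. The downside is that time since the end of treatment at the final assessment will vary somewhat between patients.
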